### Post trial care {30}

Participants will continue with services as usual post-trial.

### Measures {12} {20a}

For this study, primary outcomes concern parental SUD recovery and prevention of future substance-exposed births. Specifically, we will assess substance use (recency and frequency), SUD treatment completion, duration of abstinence from substance use, use of family planning methods, and number of subsequent substance-exposed births. Secondary outcomes concern parent–child linkage to recovery supports and social services, prevention of foster care placement, parent–child reunification, and family stability. Recovery supports/social services include housing, health care, family planning, mental health treatment, support groups, food assistance, daycare/childcare, and legal services. Prevention of foster care placement and parent–child reunification will be examined in terms of the living arrangement and legal custody of the index child and the number of months the child lived with the participant. Family stability refers to parental education and employment status, stable housing, and no new involvement with the criminal justice system.

### Data management {19}

Whenever possible, data will be directly entered into REDCap, a HIPAA-compliant data management platform. During the interview portion of the assessment, the research coordinator will enter participant responses into REDCap as they are given. When the self-administered survey is completed online, data will be stored as each question is answered. We anticipate that participants’ completing the self-administered survey on paper will be rare. When that happens, the paper forms will be stored in a locked cabinet until the data are entered by the research coordinator and data entry accuracy is verified by another study staff member, after which the paper forms will be shredded (Table 1).

**Table 1 Tab1:** Measurement instruments, constructs, and purpose {18a}

Instrument	Constructs	Measurement purpose
Addiction Severity Index	Demographics, alcohol and drug use, family planning methods, legal involvement, medical conditions, psychiatric disorders, employment, connection to community resources, family history, child custody adverse childhood experiences	Primary and secondary outcomes
Brief Version of Addiction Severity Index	Current alcohol and drug use, family planning, legal involvement, mental status, psychiatric disorders, employment, connection to community resources, child custody	Primary and secondary outcomes
Self-administered survey	Criminal justice involvement, expanded adverse childhood experiences (baseline only), social support, maternal attachment, post-traumatic stress, psychological distress, self-esteem, self-efficacy, addiction beliefs, positive parenting, knowledge of child development, benevolent child experiences, working alliance inventory	Secondary outcomes and mediators

The 5^th^ edition of the Addiction Severity Index (ASI) is a semi-structured interview instrument that assesses the following domains: medical status, employment/support status, substance use, legal status, family history, family/social relationships, and psychiatric status [33]. This instrument has been supplemented with additional items developed by subject matter experts, straightforwardly worded. These include items to assess drug use during pregnancy, reproductive history, and adverse life experiences not assessed in the ASI. Substances assessed include and expand upon those in the ASI: alcohol, heroin, fentanyl, methadone, other opiates/analgesics, barbiturates, sedatives/tranquilizers, cocaine, methamphetamine, other amphetamines, cannabis, hallucinogens, inhalants, and other substances. Additional items assess birth control use, number and living situation of biological children, adverse life experiences, and child protective services involvement. Items have also been created to assess the services participants have received in the preceding year, including healthcare for mother and child(ren), family planning, mental health, housing, emergency funds, food/clothing/supplies, legal aid, domestic violence, childcare, support groups, public schools, and public health nursing. Each service is coded as to whether the participant expressed a need for that service (yes = 1/no = 0) and whether the service was received (yes = 1/no = 0). An abbreviated (brief) version of the ASI that omits time invariant/historical information is administered at the annual follow-up assessments.

#### Self-administered survey (SAS)

The SAS was developed by the investigator team, drawing primarily upon standardized scales and measures used in addictions research and related subfields that have solid psychometric properties. The SAS elicits information from participants along several dimensions covering a wide range of participant behavior metrics and social psychological concepts important for addiction research, including criminal justice involvement, additional adverse childhood experiences (ACEs) from an expanded ACEs instrument [34], social support [35], maternal attachment (antenatal [36] and postnatal [37]), mental health (PTSD [38] and psychological distress [39]), self-esteem [40] and self-efficacy [41], addiction beliefs [42, 43], parenting practices [44], and parent/child experiences [45] and child development [46]. These measures allow us to examine both predictors of success, as well as additional secondary outcomes stemming from the intervention. Figure 2 presents the schedule of enrollment, intervention, and assessments.

**Fig. 2 Fig2:**
[figure not shown]
Schedule of enrollment, intervention, and assessments {13}

### Intervention adherence {11c} {18b}

Adherence to the intervention on the part of the participant is defined as engagement with the CM. Strategies to improve adherence will include (1) requiring the CMs to reach out proactively to participants in the intervention condition to arrange biweekly face-to-face meetings, (2) offering transportation to participants in support of their goals, (3) helping participants to access tangible goods (e.g., diapers, food assistance) in support of family needs, and (4) obtaining consent to contact a friend or family member in the event the participant cannot be reached/located.

#### Fidelity monitoring

Fidelity to the PCAP model will be monitored by examining time logs for CMs and monthly and semi-annual reports of participant status. CMs will record the amount of time spent working directly with or on behalf of each participant, including face-to-face meetings, time spent transporting the participant, phone communication with the participant, and other time spent working on a participant’s case without the participant present, such as working with an agency on behalf of the participant, time spent with participant’s family, and time spent corresponding with the participant. Specifically, we will monitor the number of visits per month, maintaining an expectation that CMs meet with each intervention participant twice per month and that CMs spend at least 55% of their time working with or on behalf of intervention participants. A case management supervisor will monitor time spent with participants and intervention milestones, providing feedback when deviations from fidelity are noted.

### Data analysis plan {20b} {20c}

After checking for equivalency between groups on key baseline measures, we will conduct cross-sectional, bivariate analyses to assess differences between treatment and control groups at 12-, 24-, and 36-month timepoints. Evaluation of effectiveness will utilize both intent-to-treat (ITT) and as-treated (AT) approaches [47]. In the ITT analysis, all randomly assigned participants will be included in the analysis, regardless of the extent to which they received the intervention. In the AT analysis, only those who remain engaged in the intervention at the timepoint of interest will be included. Additionally, we will examine the dosage of the intervention and intervention site as moderators of between-group effects. Other potential moderators to be examined include participant race/ethnicity, marital status, age, and criminal justice involvement.

We anticipate that missing data will not be missing completely at random and are unlikely to be missing at random due to the nature of SUD research. For example, participants with more severe SUDs may be more likely to die from overdose and thus contribute to missing data. We will acknowledge this limitation when the findings are disseminated. Bivariate analyses will use pairwise deletion in the case of missing data. Regression analysis examining mediation and moderation will use listwise deletion. Statistical modeling will use full information maximum likelihood estimation whenever possible.

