**Methods:**

Using an intent-to-treat design, the study will recruit from two metro areas in Oklahoma and enroll 200 birthing individuals who are pregnant or up to 24 months postpartum with at-risk substance use during their current or most recent pregnancy. Participants will be randomly assigned, stratified by location, to receive either PCAP or services as usual for 3 years. Participants in the PCAP condition will meet with their case manager approximately biweekly over the course of the intervention period, in their local communities or in their own homes whenever possible. Case managers will assist with goal setting and provide practical assistance in support of participants’ goals. Primary and secondary outcomes will be assessed at baseline and 12, 24, and 36 months post-baseline using the Addiction Severity Index interview and a self-administered survey.

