### Study design {8} {9} {14}

We will evaluate PCAP using a RCT with an intent-to-treat design in two sites in Oklahoma: Oklahoma City and Tulsa, including their surrounding areas. The study will recruit and enroll 200 participants, with 50 control and 50 treatment group participants at each site. Both groups will participate in data collection at baseline and at 12, 24, and 36 months post-baseline, with 36 months post-baseline being the primary endpoint. Study participants will not be constrained from accessing any other services or interventions that may be available in their community.

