### Randomization procedures {16a} {16b} {16c}

Group assignment will occur via an online random assignment generator called Research Randomizer [32], which relies on a computer algorithm for randomization within REDCap, the data management system described below. Randomization will be stratified by location to produce equal numbers of participants in the treatment and control groups at each site. Neither the research staff using the system nor the participant will know the group assignment before the baseline data are collected. Figure 1 displays enrollment and randomization processes.

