#### Power and sample size

The sample size of 200 participants will provide power of .80 to detect at least small-to-medium effects (Cohen’s *d* = .40) using two-tailed, between-groups, planned comparisons with an error probability of .05, reflecting the ceiling of statistical power. Given the nature of SUDs and their potential impact on the stability of participants’ lives, we conservatively estimate that 33% will attrit from the study before the primary endpoint of 36 months. This is more conservative than what has been observed in Washington State, where 72% of participants who enrolled in PCAP remained in the program for 36 months. A sample size of 132 participants will provide power of .80 to detect at least medium effects (Cohen’s *d* = .50), reflecting the anticipated floor of statistical power.

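### The treatment-control comparisons are unadjusted: valid as they stand, but precision available from baseline outcome values (and, to a small extent, from site) goes unused

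*Protocol article*

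**What the plan says.** The Data analysis plan sets the method for judging effectiveness: "we will conduct cross-sectional, bivariate analyses to assess differences between treatment and control groups at 12-, 24-, and 36-month timepoints". The step before it is described as "After checking for equivalency between groups on key baseline measures", and no other use of baseline data in these comparisons is given. Site appears once in that section, as an additional analysis: "we will examine the dosage of the intervention and intervention site as moderators of between-group effects". Regression is mentioned for mediation and moderation. Full information maximum likelihood is mentioned for statistical modelling in general and is not tied to the comparison of arms.

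The design supplies what these comparisons leave out. Under Randomization procedures, "Randomization will be stratified by location to produce equal numbers of participants in the treatment and control groups at each site". The abstract's Methods paragraph says "Primary and secondary outcomes will be assessed at baseline and 12, 24, and 36 months post-baseline". The Study design section makes 36 months the primary endpoint. The Power and sample size section rests on a plain two-sided comparison between groups.

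**The concern.** A bivariate test of outcome by arm has no place for a covariate. Two pieces of information known before randomisation are therefore left out of the main contrast.

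- **Baseline value of the outcome.** Where it predicts the 36-month value, leaving it out keeps explainable variation in the error term. At 66 per arm the standard error of a baseline difference is √(2/66) = .174 SD, so differences up to about 1.96 × .174 = .34 SD are within ordinary chance. The unadjusted estimate carries such a difference forward in proportion to r. An equivalency check can reveal the difference but does not remove it.
- **Site.** Stratified randomisation balances arms within site. If outcomes differ by site, an analysis that omits site gives a standard error that is slightly too large.

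Precision matters here because the trial expects to lose a third of its participants and then to detect only medium effects.

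**Working it through.** **Inputs from the article.** 200 participants, 1:1 ("The study will recruit and enroll 200 participants, with 50 control and 50 treatment group participants at each site"); two-sided error probability .05; power .80 for d = .40 at N = 200 and for d = .50 at N = 132; 33% attrition by 36 months. No baseline-to-follow-up correlation or R² is given, so r is an assumption throughout.

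**Step 1: reproduce the stated power.** For n per arm and SD 1, power ≈ Φ(d√(n/2) − 1.96).

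- N = 200, d = .40: .40 × √50 = 2.828; less 1.960 = .868; power .807 (t-test .804).
- N = 132, d = .50: .50 × √33 = 2.872; less 1.960 = .912; power .819 (t-test .814).

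Both agree with the stated .80. Attrition of 33% from 200 leaves 134, within two of the stated 132. At 66 per arm the effect detectable with 80% power is d = .491 (t-test).

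**Step 2: adjust for a baseline value.** With correlation r, the residual SD is √(1 − r²). Detectable d is multiplied by √(1 − r²), and the unadjusted test needs 1/(1 − r²) times as many participants for the same precision. The power columns use the normal approximation.

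| Assumed r | Equivalent extra participants | 132 act like | Detectable d, N = 132 | Power, d = .50, N = 132 | Power, d = .40, N = 200 |
|---|---|---|---|---|---|
| 0 (unadjusted) | – | 132 | .49 | .82 | .81 |
| .1 | 1% | 133 | .49 | .82 | .81 |
| .2 | 4% | 138 | .48 | .83 | .82 |
| .3 | 10% | 145 | .47 | .85 | .84 |
| .5 | 33% | 176 | .43 | .91 | .90 |
| .6 | 56% | 206 | .39 | .95 | .94 |

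For r = .3, for example: 1/(1 − .09) = 1.099, and .491 × .954 = .469.

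**Step 3: adjust for site alone.** With two equal sites differing by δ (in units of the within-site SD), R² = (δ/2)²/(1 + (δ/2)²), so 1/(1 − R²) = 1 + (δ/2)². For assumed δ = .2, .3 and .5 this is 1.010, 1.023 and 1.063, or about 1%, 2% and 6%. Nearly all the gain in prospect therefore comes from the baseline value.

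**Step 4: which primary outcomes can benefit.** Of those listed under Measures, recency and frequency of substance use and use of family planning have a baseline counterpart. Treatment completion during the trial and the number of subsequent substance-exposed births have no direct one. The formula in Step 2 is for continuous outcomes and only approximate for binary or count outcomes.

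**The case against.** The strongest reply is that nothing is wrong. An unadjusted comparison of randomised arms is valid, the power statement rests on that same comparison, and it reproduces. That stands: this is neither a bias nor a sample-size error.

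A second reply is that a condensed article leaves model covariates to a fuller plan. This has less force, because the article does not leave the method open. It names a bivariate comparison and assigns regression to other purposes. The general remark on statistical modelling does not change that.

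Several stronger readings are tempting and not supported:

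- **That the plan forfeits a known 10% to 33% of its sample.** Those figures are r = .3 to .5 and nothing else. Over three years r could be lower, and at r = .2 the gain is 4%. They also do not extend to outcomes without a baseline value.
- **That site is ignored.** It is examined as a moderator. That asks whether the effect differs by site and does not adjust the main contrast, but site is not absent.
- **That the equivalency check is a significance test of baseline differences.** The text names no test.
- **That pregnancy status at entry must be a covariate.** The article gives no figures showing that substance use or contraception differs at baseline between pregnant and postpartum participants. A two-level covariate would also leave out the alternative eligibility route in the Screening section, for people who have a child with Fetal Alcohol Spectrum Disorder and may be neither pregnant nor recently postpartum.

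**Conclusion.** The point holds as one of efficiency. The comparisons of arms are written as unadjusted, although the stratification factor and baseline values of some primary outcomes will be on file. For continuous outcomes with a baseline value, and assuming r = .2 to .5, adjustment is worth about 4% to 33% more participants and lowers the detectable effect at N = 132 from d = .49 to between .48 and .43. The true figure depends on a correlation that the article does not give. Site contributes a few percent at most under the assumed differences and belongs in the model mainly because randomisation was stratified on it.

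A reader might infer that the trial is underpowered or its estimate biased because it is unadjusted. The documents do not support either. Nor would adjustment cure the non-random dropout that the article itself anticipates. This is a free improvement.

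**What to change.** State that the primary 36-month intent-to-treat comparison is a regression suited to the outcome type (linear, logistic or count) on arm, site and, where one exists, the baseline value of the same outcome. Report adjusted mean or risk differences. For treatment completion and subsequent substance-exposed births, adjust for site and, at most, one other prespecified baseline covariate.

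Fix the covariate list before any comparison of outcomes by arm, and do not choose covariates from the equivalency check. The timing matters because the Data and safety monitoring section has the investigators reviewing outcomes semi-annually. Keep the baseline comparison as description and the unadjusted contrast as a supporting result.

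The cost is analysis wording only: baseline outcomes and site are already collected, and no participants or visits are added.

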### Description of the intervention {11a} {11b} {11d}

The Parent–Child Assistance Program (PCAP) has been described in detail elsewhere [25, 28]. In brief, PCAP is a 3-year intervention for pregnant and post-partum individuals with problematic or at-risk substance use during their most recent pregnancy. Built on the theoretical foundations of relational theory [29], the transtheoretical model of behavior change [30], and harm reduction [31], PCAP aims to support birthing individuals in completing SUD treatment and link them with comprehensive community resources to help them stay in recovery, build healthy lives, and avoid exposing any future children to alcohol or drugs prenatally. PCAP provides program participants with a bachelor’s-level case manager (CM), with whom they meet approximately bi-weekly, in participants’ own homes or elsewhere in the community. CMs typically work with up to 20 participants and their families, serve as role models, help them to articulate their own goals and take steps to reach them, and provide transportation and practical assistance when needed in support of participants’ goals. The intervention manual is available at https://pcapwa.org/manual. There are no formal criteria for modifying the intervention for a given participant. The design of the intervention provides for flexibility to adjust the frequency of contacts according to the participant’s needs and preferences while aiming for an average of two face-to-face contacts per month over the course of the intervention. Consistent with the intent-to-treat approach, participants who ask to suspend their participation in the intervention or withdraw from the intervention completely will remain in the study unless they specifically ask to withdraw from the study as a whole.

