### Description of the control condition {6b}

Participants randomly assigned to the control condition will not receive PCAP but will not be constrained from accessing available services as usual in their community. They will be provided with a list of local services and resources. These resources include information for accessing substance use disorder and mental health treatment and support, health care, family planning, domestic violence services, housing and food assistance, and legal services.

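### An as-treated analysis stands unranked beside ITT as evidence of effectiveness, and dosage is a moderator, although engagement and dosage exist only in the PCAP arm

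*Protocol article*

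**What the plan says.** All of the following is in the protocol article.

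- **Two analysis approaches, not ranked.** The section Data analysis plan states: "Evaluation of effectiveness will utilize both intent-to-treat (ITT) and as-treated (AT) approaches". For ITT, "all randomly assigned participants will be included in the analysis, regardless of the extent to which they received the intervention". For AT, "In the AT analysis, only those who remain engaged in the intervention at the timepoint of interest will be included". The section does not call AT supportive and names no adjustment for selection into engagement.
- **Dosage as a moderator.** The same paragraph adds that "we will examine the dosage of the intervention and intervention site as moderators of between-group effects".
- **What engagement is.** Under Intervention adherence: "Adherence to the intervention on the part of the participant is defined as engagement with the CM", CM being the PCAP case manager.
- **How dosage is recorded.** Under Fidelity monitoring: "CMs will record the amount of time spent working directly with or on behalf of each participant".
- **Control exposure.** Under Description of the control condition: "Participants randomly assigned to the control condition will not receive PCAP".
- **What drives contact frequency.** Under Description of the intervention, the design "provides for flexibility to adjust the frequency of contacts" according to what each participant needs and prefers.

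The abstract and the Study design section label the trial intent-to-treat, and Study design makes 36 months the primary endpoint.

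**The concern.** Staying engaged is something a participant does after assignment, and only a PCAP participant can do it. Restricting the PCAP side to those still engaged, and setting them against controls who have passed no matching filter, compares groups that randomisation did not create. Any characteristic that affects both staying with the case manager and the outcome will then appear as a treatment effect. The Data analysis plan itself expects loss to be related to the severity of the substance use disorder, so such a characteristic is plausible.

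Dosage has a related problem. A moderator analysis asks how the arm difference changes across levels of the moderator, which requires controls at those levels. No control has any PCAP dosage. What remains is an association within the PCAP arm, and because contact is adjusted to the participant, that association is confounded in a direction that cannot be known beforehand.

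The results are to go to federal clearinghouses that rate strength of evidence. While ITT and AT are unranked, the plan does not say which conclusion holds if AT is favourable and ITT is null.

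**Working it through.** **1. The plan's own figures.** The section Power and sample size gives power of .80 for d = .40 with 200 participants and for d = .50 with 132 (two-sided .05). Normal approximation: power = Φ(d/√(2/n) − 1.960), with n per arm.

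- n = 100, d = 0.40: 0.40/√0.02 = 2.828, and Φ(0.868) = 0.807 (0.804 by noncentral t).
- n = 66, d = 0.50: 0.50/√(2/66) = 2.872, and Φ(0.912) = 0.819 (0.814 by noncentral t).

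Both reproduce the stated .80. They concern the comparison of randomised arms. The article gives no figure for AT or dosage.

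**2. Bias of the AT contrast with no true effect.** From the documents: 100 per arm, and 72% programme retention at 36 months in Washington State. Assumed: the engaged are the upper share p of a latent trait that correlates ρ with the outcome, and all 100 controls are analysed without loss. The documents give no ρ, so a range is shown.

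Bias in SD units = ρ·φ(c)/p, with c = Φ⁻¹(1 − p). For p = 0.72, c = −0.583, φ(c) = 0.337 and φ(c)/p = 0.468. False-positive rates come from 20,000 simulated trials per setting, using a two-sample t test at two-sided 0.05.

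| ρ (assumed) | Bias, 72% engaged | False positives | Bias, 50% engaged (assumed) | False positives |
|---|---|---|---|---|
| 0 | 0 | 5% | 0 | 5% |
| 0.1 | 0.05 | 6% | 0.08 | 8% |
| 0.2 | 0.09 | 9% | 0.16 | 15% |
| 0.3 | 0.14 | 15% | 0.24 | 28% |
| 0.5 | 0.23 | 34% | 0.40 | 66% |

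At 72% engaged and ρ = 0.5, the bias is 0.23/0.50 = 47% of the effect for which the trial has its floor of power.

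**3. Adding loss among controls.** The article expects 33% study attrition. Suppose 67% of controls are retained on the same latent trait with the same ρ. Then c = −0.440, φ(c) = 0.362, and the control mean shifts by (0.362/0.67)ρ = 0.541ρ. The net bias is 0.468ρ − 0.541ρ = −0.073ρ, which is −0.04 SD at ρ = 0.5. This is also an assumption, since control dropout may select less strongly, but it shows that the sign can change.

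**4. Dosage.** Write Y = β0 + β1A + β2D + β3(A×D), with A the arm and D the dosage. D = 0 whenever A = 0, so A×D = D for every participant. The two columns are identical, and β2 and β3 cannot be separated. The conclusion does not depend on this model form, because no method can estimate an arm difference at a non-zero dosage at which no control exists.

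**The case against.** The strongest reply is that the randomised comparison is already in the plan. ITT is named first and covers everyone randomised, the design carries the ITT label, people who leave the intervention stay in the study, and the 36-month endpoint is fixed. Dosage is introduced as an additional analysis and not as a test of effectiveness. All of this stands. A reader might infer that effectiveness will be judged on AT and dosage instead of ITT, or that AT could override ITT. The documents say neither.

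A second reply is that a condensed article leaves the control-side AT rule and the dosage model to a statistical analysis plan that is not shown. This stands in part. Read literally, the AT sentence leaves no controls in the analysis set. That reading is implausible beside the plan to compare treatment and control groups, and the point does not rest on it. But the AT restriction and the choice of dosage as a moderator are stated rules, not omitted detail, and an analysis plan that follows them inherits the problem.

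A third reply is that the bias is not established. It depends on an assumed correlation, on a retention figure from another state's programme, and on no loss among controls. This also stands. A reader might infer from the table that AT will favour PCAP, or will be wrong by 0.23 SD. Step 3 of the working shows why that does not follow.

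**Conclusion.** The point holds in a limited form. The plan has a valid ITT analysis but does not rank it above an AT contrast that lacks the protection of randomisation. It also names as a moderator of between-group effects a variable with no counterpart among controls. Both conclusions follow from the protocol's own definitions and need no numerical assumption.

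The size is illustrative only. With no true effect, 72% engaged, no control loss and assumed correlations of 0 to 0.5, the bias runs from 0 to 0.23 SD and the false-positive rate from about 5% to 34% against a nominal 5%. Severity-related loss among controls could shrink or reverse this. What the documents establish is that the AT contrast carries no guarantee of being unbiased, not that it is biased in PCAP's favour. The sample-size figures are unaffected.

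**What to change.** 1. State in the Data analysis plan that ITT at 36 months, already the primary endpoint, is the sole basis for the effectiveness conclusion. Label any AT result as supportive and non-randomised.
2. Remove dosage from the moderators of between-group effects and report it descriptively within the PCAP arm. Site can stay as a moderator.
3. If an effect of receiving PCAP is wanted, replace AT with a complier average causal effect using random assignment as the instrument. Because controls do not receive PCAP, non-compliance is one-sided. Define compliance in advance from the contact logs as initiation or a minimum exposure. Engagement at the timepoint will not serve, because someone who leaves late has had substantial exposure but would count as a non-complier. State the exclusion restriction, namely that assignment has no effect on the outcome of non-compliers.

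**Cost.** Items 1 and 2 are wording. Item 3 needs modest extra analysis and no new data, but it relies on the exclusion restriction and gives a wider interval. For illustration, with 100 per arm, SD 1, no loss and 72% compliers, the standard error is about √(2/100)/0.72 = 0.196. This compares with √(2/100) = 0.141 for ITT and √(1/72 + 1/100) = 0.155 for the AT contrast. A higher complier share, as an initiation rule would be likely to give, narrows that gap.

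### The 36-month intent-to-treat comparison drops unobserved participants by pairwise deletion, although the plan itself doubts that data will be missing at random

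*Protocol article*

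**What the plan says.** The protocol article, Data analysis plan {20b} {20c}, tests effectiveness by cross-sectional bivariate comparisons of the two arms at 12, 24 and 36 months. Study design {8} {9} {14} makes 36 months the primary endpoint. On missing data the analysis section says:

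- Mechanism: "We anticipate that missing data will not be missing completely at random and are unlikely to be missing at random". Its example is that people with more severe disorders may die of overdose and so add to the missing data. The response stated directly after this is to acknowledge the limitation on publication.
- Rule for the group comparisons: "Bivariate analyses will use pairwise deletion in the case of missing data".
- Rules for other analyses: listwise deletion for mediation and moderation regressions, and full information maximum likelihood (FIML) for statistical modelling where possible.
- Intent-to-treat set: "all randomly assigned participants will be included in the analysis, regardless of the extent to which they received the intervention".

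Power and sample size adds "we conservatively estimate that 33% will attrit from the study before the primary endpoint of 36 months" and bases its lower power figure on 132 participants.

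**The concern.** Pairwise deletion in a single-outcome comparison at one visit keeps everyone assessed at that visit and drops everyone else. In general it is justified only when data are missing completely at random, which the plan rejects. So the plan gives its primary-endpoint comparison a method whose justifying condition it says will fail.

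Two consequences follow. First, about a third of those randomised would be absent from an analysis described as containing all of them. Second, someone who dies of overdose leaves the comparison, although the primary outcomes include substance use and duration of abstinence, for which such a death is hard to regard as uninformative.

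What matters is the difference between arms. Unequal loss is plausible: under Intervention adherence {11c} {18b}, case managers reach out to PCAP participants to arrange biweekly meetings, and controls have no case manager. If the people lost do worse and more of them are lost from one arm, that arm looks better than it is.

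**Working it through.** **The plan's own figures.** Inputs: "The study will recruit and enroll 200 participants, with 50 control and 50 treatment group participants at each site", so 100 per arm; two-sided 0.05; d = 0.40 at 200 and d = 0.50 at 132. Normal approximation: power = Φ(d·√(n/2) − 1.96), with n per arm.

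- n = 100, d = 0.40: 0.40 × √50 = 2.828; Φ(0.868) = 0.807.
- n = 66, d = 0.50: 0.50 × √33 = 2.872; Φ(0.912) = 0.819.

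Both agree with the stated 0.80. A 33% loss leaves 200 × 0.67 = 134; the stated 132 is a 34% loss, a trivial gap. The lower power figure shows that the plan itself expects the 36-month comparison to rest on about two-thirds of those randomised.

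**Binary illustration, no true effect.** Assumptions not in the documents: 50% abstinent in each arm, the split of loss by arm (averaging 33%), and abstinence q among those lost. With loss a, the observed rate is (0.50 − a·q)/(1 − a). Differences are taken before rounding.

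| Loss, PCAP / control | q | PCAP observed | Control observed | Apparent difference |
|---|---|---|---|---|
| 33% / 33% | 0.20 | 64.8% | 64.8% | 0 |
| 28% / 38% | 0.10 | 65.6% | 74.5% | −9.0 points |
| 28% / 38% | 0.20 | 61.7% | 68.4% | −6.7 points |
| 28% / 38% | 0.30 | 57.8% | 62.3% | −4.5 points |
| 23% / 43% | 0.20 | 59.0% | 72.6% | −13.7 points |

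For scale, take 66 per arm and 50% against 73.5%. The pooled rate is 0.6175, the null standard error √(2 × 0.6175 × 0.3825/66) = 0.0846, and the alternative standard error √((0.25 + 0.1948)/66) = 0.0821. Power is Φ((0.235 − 1.96 × 0.0846)/0.0821) = Φ(0.84) = 0.80. The detectable difference is thus about 23.5 points, and a bias of 4.5 to 9 points is 19% to 38% of it.

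**Continuous illustration, no true effect.** Bias = m_T·δ_T − m_C·δ_C, where m is the fraction missing and δ is the observed mean minus the missing mean, in SD, with higher scores better. All δ values are assumed.

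| Missing, PCAP / control | δ, PCAP / control | Bias | Type I error |
|---|---|---|---|
| 33% / 33% | 0.5 / 0.5 | 0 | 0.05 |
| 28% / 38% | 0.5 / 0.5 | −0.05 SD | 0.06 |
| 33% / 33% | 0 / 0.5 | −0.165 SD | 0.16 |
| 33% / 33% | 0.5 / 0 | +0.165 SD | 0.16 |

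The last two rows show that equal loss does not protect the comparison when the reasons for loss differ, and that the bias can run either way.

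**The case against.** The best defence is that data missing not at random do not by themselves bias the difference between arms. Under the null, like missingness in both arms gives zero bias, and a modest imbalance may do little (0.05 SD and type I error 0.06 above). The documents give no attrition by arm. This stands, and it limits the point to exposure to bias.

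It can also be said that the intent-to-treat sentence is about adherence, and that the reduced sample is disclosed in the power section. That is fair as to intent, but the sentence still says that all randomised participants are analysed, and under deletion they are not.

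Sensitivity analyses may sit in an analysis plan that is not shown, so their absence is not the fault here. The deletion rule, however, is stated. FIML does not answer it: it is assigned to modelling rather than to the bivariate comparisons, and it relies on missing at random.

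A reader might infer four stronger points that the documents do not support:

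- *The result will be biased, against PCAP.* Neither size nor direction can be known from the documents.
- *The listwise and FIML rules contradict each other.* The wording is loose, but they are attached to differently named analyses, and neither governs the group comparison.
- *The 12- and 24-month data are thrown away.* They are analysed at their own timepoints; they are only unused for the 36-month contrast.
- *Controls cannot be traced as well, because of* "obtaining consent to contact a friend or family member in the event the participant cannot be reached/located". The article lists this as an adherence strategy and does not say that controls lack such a contact. Assessment procedures has research staff check in with both groups every 3 months to keep contact details current.

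**Conclusion.** The point holds in limited form. The plan assigns deletion to its primary-endpoint comparison while stating that the condition justifying deletion will not be met. It classes overdose deaths as missing, and it describes as complete an analysis that it expects to cover about 132 of 200 participants. That is a fault in stated text.

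The effect on the result is a risk of unknown size and sign. It is zero under the null with like missingness, and 4.5 to 9 points under the assumed 28%/38% loss with 50% true abstinence and 10-30% abstinence among those lost. The 23%/43% row needs a 20-point gap in attrition and should not be read as a forecast. As specified, the comparison offers no means of judging where in this range the trial falls.

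**What to change.** 1. For the between-group intent-to-treat comparisons, replace pairwise deletion with a longitudinal likelihood-based model, or multiple imputation for binary and count outcomes. Include all randomised participants and use baseline, 12- and 24-month data to inform the 36-month contrast.
2. Because this still relies on missing at random, add delta-adjusted (tipping-point) sensitivity analyses with separate shifts for each arm. Setting every missing value to substance use is no neutral substitute as a sole analysis: in the 28%/38% example with q = 0.20 it gives 0.50 − 0.28 × 0.20 = 44.4% against 0.50 − 0.38 × 0.20 = 42.4%, a false 2-point PCAP benefit.
3. State how death enters each substance-use and recovery outcome, for example as an unfavourable result, at least in a sensitivity analysis. This is a choice of estimand and should be made explicitly.
4. Call any analysis restricted to observed participants available-case.

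The cost is analyst time and a protocol amendment, with IRB submission and, if judged major, a registry update as set out under Protocol amendments {25}. No further participants or data collection are needed. Enrolment began in December 2022, so the first 36-month assessments fall due from December 2025; the change should be fixed and dated before the 36-month comparison is run.
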